#### Relevant concomitant care permitted or prohibited during the trial {11d}

The use of psychopharmaca during the group therapy is permitted. In order to strengthen the clinical validity of the trial and to provide good clinical care in case of comorbidity, a limited amount (maximum 10 sessions) of the following psychotherapeutic co-interventions is allowed: EMDR, family or couple therapy or relapse prevention for substance abuse. The decision of adding a co-intervention must be made by the research committee and is monitored. Sensitivity analyses will be performed with these interventions as a covariate. Extra health care costs are incorporated in the cost-effectiveness analysis.

#### Provisions for post-trial care {30}

After termination of the treatment, a period of 6 months without psychotherapy is strongly advised. If for any reason additional care is necessary before these 6 months, the patient can reapply for therapy at the NPI, with a referral by the GP. In this case of reapplication, the research committee must be informed and can be involved in the decision making about the following therapy. If the patient reapplies after 6 months, but before the follow-up measurements are conducted, the same procedure is applicable.

No risk of harm is expected by participating in this trial.

### Outcomes {12}^2^

Baseline assessment takes place right after informed consent and before randomization and start of treatment. Assessments consist of digital questionnaires and semi-structured interviews and are all administered in Dutch. Assessors are trained and will be supervised to ensure quality of data collection of semi-structured interviews. Table 1 shows an overview of the instruments per assessment point.

**Table 1 Tab1:**
[figure not shown]
Overview of study design, measurements, and time of assessment

^a^SFGT

^b^PG

#### Primary outcome

The primary outcome is severity of Cluster-C personality pathology measured by the Assessment of DSM-IV Personality Disorders questionnaire (ADP-IV*,* [79]. With this self-report questionnaire, DSM-IV PD criteria are assessed, but because in DSM-5 no important changes are made in the description of PDs, the ADP-IV is still applicable. Patients indicate on a 7-point Likert scale to what degree PD criteria hold for them, ranging from 1 (‘not at all’) to 7 (‘completely’), and whether they experience distress from it (on a range from 1-not at all to 3-definitely). Item construction of the ADP-IV allows for both dimensional and categorical diagnostic evaluation [79]. Adequate internal consistency, validity and reliability were shown consistently in previous studies [28, 78]. A selection of the Cluster-C items from the ADP-IV is made for the primary outcome measure of this trial.

#### Secondary outcomes

##### Personality functioning

With the aim of capturing the complexity of personality functioning, this concept is measured in three ways. First, to explore the predictive value of amount of personality traits (Cluster-C and comorbid PD traits) and to measure remission rates of the Cluster-C personality disorder, the Structural Clinical Interview for DSM-5 personality disorders (SCID-5-P-NL, [4] is used*.* The Dutch version of the SCID-5-P is used for diagnosing PDs at assessment and at 24 months. The exact reliability and validity of the SCID-5-P is unknown, but research has shown that both the original SCID-II and the Dutch version and translations of the SCID-5-P in other languages have adequate to good interrater reliability and test–retest interrater reliability [41, 59, 66, 81] Assessment using the SCID-5-P will be guided by items previously affirmed by the patient on the Structured Clinical Interview for DSM-5 Personality Questionnaire (SCID-5-PV), a self-report questionnaire screening for PDs that will be completed at intake. Items not affirmed on the SCID-5-PV will be assumed to be true negatives; however, if a clinician has reason to believe these are false negatives, such items will be assessed. This method is in accordance with instructions for using the SCID-5-P and enables the assessment of PD symptoms to be based upon self-report combined with a structured clinical interview.

Secondly, the severity of the primary Cluster-C PD is measured with the Avoidant Personality Disorder Severity Index (AVPDSI), Dependent Personality Disorder Severity Index (DEPDSI) or the Compulsive Personality Disorder Severity Index (OCPDSI), the choice depending on what the primary PD is. These semi-structured interviews are developed to assess the frequency and severity of manifestations of the DSM-5 criteria of avoidant, dependent and compulsive PDs. The recall period for these instruments is 3 months. For patients with a main diagnosis 'otherwise specified PD' with predominantly Cluster-C traits, a personalized selection of the Cluster-C traits derived from the AVPDSI, OCPDSI and DEPDSI is made. Psychometric qualities of these instruments are still under research, but excellent interrater agreement (ICC > 0.90) and internal consistency (Cronbach’s *a* > 0.90) is established [43]. Total scores of the AVPDSI, DEPDSI and OCPDSI consist of a total sum of the average symptom scores per subsection of the interview, an average burden score and an average impact score. The scores on the instruments are converted into one severity score by standardizing the raw scores (see [43]).

To ensure quality of data collection of this developed instruments, assessors will be trained and supervised, and all measurements will be audiotaped.

Third, the change in global severity of personality pathology according to Kernberg’s object-relationship framework is measured by the Inventory of Personality Organisation Short Form (IPO-16-NL, [48]. The IPO-16-NL is the Dutch short version of the IPO-83 [20]. Norm scores of the German version are available and psychometric evaluation has shown good internal consistency, reliability, validity and confirmed a one factor structure of general personality dysfunction [106, 107]. The total score on the 16 items represents a dimensional measure of global severity of personality pathology.

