### Eligibility criteria {10}^1^

#### Inclusion criteria

Primary diagnosis DSM-5 diagnosis of a Cluster-C PD or otherwise specified PD with predominantly Cluster-C traits (operationalized as a minimum of 5 Cluster-C traits).Age 18–65 yearsThe willingness and ability to participate in a group treatment of 1–2 years.A written informed consent.

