## Assignment of interventions: blinding

### Who will be blinded {17a}

Because the study is a clinical psychotherapy trial, it is not possible to blind therapists and participants. However, the research assistants who perform the baseline assessments will be blind for treatment allocation. Also, the other assessments that contain diagnostic interviews are conducted by blinded research assistant. In this way, knowledge about the type of treatment will not affect the outcome of the assessment.

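### The 24-month SCID-5-P follows the entry rule, guided by a screener completed at intake, so the absolute remission rate may be biased upward

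*Protocol article*

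**What the plan says.** All of the rule stands in the Protocol article, Secondary outcomes, under Personality functioning.

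- One purpose of the SCID-5-P is "to measure remission rates of the Cluster-C personality disorder".
- It is given twice: "The Dutch version of the SCID-5-P is used for diagnosing PDs at assessment and at 24 months".
- The method is stated once, with no separate rule for follow-up: "Assessment using the SCID-5-P will be guided by items previously affirmed by the patient" on the SCID-5-PV, which is "a self-report questionnaire screening for PDs that will be completed at intake".
- The default for the remaining items is "Items not affirmed on the SCID-5-PV will be assumed to be true negatives". The same sentence adds an exception: "if a clinician has reason to believe these are false negatives, such items will be assessed".
- The article says that this way of working agrees with the instrument's own instructions.

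Under Who will be blinded, the baseline assessors are blind to allocation, and after that "the other assessments that contain diagnostic interviews are conducted by blinded research assistant".

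**The concern.** A screener shortcut is a reasonable way to reach a diagnosis at entry, because the questionnaire and the interview describe the same period. It is less suited to an outcome measured two years later. If the 24-month interview is still steered by the intake questionnaire, items affirmed at intake are asked again and can be lost or gained. Items not affirmed at intake are scored absent by default, although they may have become present since.

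Remission means that too few criteria remain. An error that can only remove criteria from the count can only add remissions. The rate concerned is the most readable clinical result of the trial, and patients and clinicians will take it at face value.

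**Working it through.** The article gives no remission rate, so there is no figure of the plan to reproduce. The check has two parts: what the rule implies at 24 months, and how large the effect could be.

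**The rule at 24 months**

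1. The screener is placed at intake. The visible text mentions no repeat, and Table 1, which lists the instruments per time point, is not shown.
2. The override is triggered by suspicion of a false negative. A trait that was truly absent at intake and emerged later was not a false negative on the screener, so the wording does not clearly reach it.
3. The override belongs to a clinician. The 24-month diagnostic interview belongs to a blinded research assistant. Whether that assistant may or must use the override is not stated.

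**Direction and size**

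All inputs here are assumptions; none is in the article. Take one disorder with 7 criteria and a threshold of 4. Of the 7 items, *a* are present at baseline, *b* were affirmed on the screener but rated absent, and *c* were not affirmed.

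- X ~ Bin(a, p): baseline traits that persist, p = 0.5 to 0.7.
- Y ~ Bin(b, 0.10): affirmed-but-absent items that turn positive. These are always asked.
- Z ~ Bin(c, q): unaffirmed items present at 24 months, q = 0 to 0.10.
- Z′ ~ Bin(c, q·o): the part of Z that is found, where o is the probability that the override catches it.

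True remission = P(X + Y + Z < 4). Recorded remission = P(X + Y + Z′ < 4). Because Z′ never exceeds Z, recorded remission is never below true remission.

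Worked case: a = 4, b = 1, c = 2, p = 0.7, q = 0.10. Let W = X + Y.

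- P(W ≤ 3) = 1 − 0.2401 − 0.1 × 0.4116 = 0.7187
- P(W ≤ 2) = 0.3483 − 0.1 × 0.2646 = 0.3218
- P(W ≤ 1) = 0.0837 − 0.1 × 0.0756 = 0.0761
- True remission: 0.81 × 0.7187 + 0.18 × 0.3218 + 0.01 × 0.0761 = 0.641
- Recorded, no override (o = 0): 0.719, an excess of 7.8 points
- Recorded, o = 0.5: 0.9025 × 0.7187 + 0.095 × 0.3218 + 0.0025 × 0.0761 = 0.679, an excess of 3.9 points
- Recorded, o = 1: 0.641, no excess

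Range over a/b/c = 5/1/1, 5/0/2 and 4/1/2, and p = 0.5 and 0.7, in percentage points:

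| q | no override | override catches half |
|---|---|---|
| 0 | 0 | 0 |
| 0.02 | 0.6–1.6 | 0.3–0.8 |
| 0.05 | 1.5–3.9 | 0.7–2.0 |
| 0.10 | 2.9–7.8 | 1.5–3.9 |

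The excess grows with the number of unaffirmed items. As an illustration, take a count over all Cluster-C items: 23 assumed, of which 6 are present, 5 affirmed but absent and 12 unaffirmed, with remission taken as fewer than 5. With no override the excess is about 6 points at q = 0.02, 13–15 at 0.05 and 23–30 at 0.10. The article does not say that remission is judged by such a count, so this shows sensitivity only.

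**The case against.** The strongest reply is that the paragraph describes entry. The intake clinician does the SCID-5-P under Recruitment, the override speaks of a clinician, and Data management promises an operating procedure for each assessment, which may hold the follow-up method. A repeat of the screener at 24 months cannot be excluded while Table 1 is not visible. In the calculation, a repeat removes the excess if patients affirm every trait they then have. This stands as a reason for caution. It does not settle the point, because the article names the 24-month interview in the same paragraph and gives it no other rule. Agreement with the instrument's instructions does not show that a two-year-old screener is a sound filter for an outcome.

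Four stronger readings are tempting, and the documents do not support them.

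- *Traits can disappear but hardly appear.* Items affirmed at intake and rated absent at baseline are asked again and can turn positive, and the override exists.
- *Remission is overstated.* This needs traits on unaffirmed items that lift a patient back over the threshold and are not caught. The article gives no rate for either.
- *The comparison between arms is distorted.* The rule is the same in all three arms. The contrast shifts materially only if the emergence or detection of such traits differs by arm, and nothing in the article shows that.
- *A patient who keeps five Cluster-C traits counts as remitted while still meeting the entry category* "otherwise specified PD with predominantly Cluster-C traits (operationalized as a minimum of 5 Cluster-C traits". The article does not define remission operationally, and that detail is commonly left to the full protocol or the analysis plan.

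**Conclusion.** The point holds as a risk of one-sided error in a secondary outcome. As written, the 24-month SCID-5-P uses the entry rule with an intake screener, and the override is not clearly fit for follow-up. If that is what is done, the absolute remission rate may be too high in all arms and cannot be too low for this reason.

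The size is unknown. For a single 7-criterion disorder it is 0 to about 8 percentage points with no override and 0 to about 4 with a 50% override, under assumed rates of 0 to 10% for traits present on unaffirmed items. It is zero if no such trait is present or if every one is caught. The ADP-IV primary outcome does not pass through the screener and is unaffected.

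**What to change.** At 24 months, have the blinded assessor rate all Cluster-C criteria of the SCID-5-P in every patient, regardless of any screener response, whether from intake or repeated. Keep the screener shortcut for Cluster A and B only. Put this in the protocol and in the operating procedure for the interview. Flag patients already interviewed at 24 months under the shortcut, and report remission with and without them as a sensitivity analysis. Recruitment began in October 2020, so some of these interviews may already have been done.

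The cost is a somewhat longer interview at a visit that is already scheduled. The baseline trait count was obtained with the shortcut, so it will not be fully comparable with the complete 24-month count, and the report should say so. Reported remission may be slightly lower.

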##### Psychiatric symptoms

The Brief Symptom Inventory (BSI, [23] is a 53-item self-report instrument that will be used to measure general psychological distress. The answers are scored on a 5-point Likert scale. It is derived from the SCL-90-R and has demonstrated it to be an acceptable short alternative of its longer version [25].

##### Quality of life, happiness, and psychosocial functioning

Quality of life is measured using the EQ-5D-5L [45]. This self-report questionnaire assesses general quality of life using five domains: mobility, self-care, usual activities, pain/discomfort and anxiety/depression. Each dimension has 5 response levels: no problems, slight problems, moderate problems, severe problems and extreme problems. The Dutch norm scores will be used for calculating the mean EQ-5D utility values [95]. The reliability of the EQ-5D-5L is found to be acceptable [45].

The Happiness Question is added as a single question on general happiness in the months prior to the assessment and is scored on a seven-point Likert scale [94]. This scale consists of different states of happiness ranging from completely unhappy to completely happy. Norms for all participating countries are available. For a single happiness item, high test–retest reliability (*r* = 0.86) and good concurrent, convergent and divergent validity have been reported. The Happiness Question [26] has excellent sensitivity to change for patients with borderline PD who were treated with group schema therapy (GST).

Psychosocial functioning and participation is assessed with the World Health Organization Disability Assessment Schedule 2.0 (WHODAS 2.0, [89], a general measure of functioning and disability in major life domains, including understanding and communication, getting around, self-care, getting along with others, life activities and participation in society.

##### Costs

Costs are assessed using a specifically adapted version of the TiC-P [93]. The TiC-P FORCE is a 14-item self-report questionnaire to assess health care costs (part I) and costs resulting from productivity losses (part II) associated with psychiatric disorders. In part I, the number of contacts with different health care providers over the last 6 months is assessed. Part II consists of items regarding absenteeism from paid and unpaid work and presenteeism (i.e. reduced productivity while at work) in the last 6 months.

#### Potential predictors and moderators

Apart from general potential predictors (sociodemographic variables, severity of psychiatric symptoms, type of PD, severity of PD), four specific potential moderators are defined and explained earlier: early childhood trauma, personality organization, autism traits and vulnerable narcissism.

Early childhood trauma is measured by the Childhood Trauma Questionnaire-Short Form (CTQ-SF) [13]. The short form was developed from the original 70-item version [12] and consists of 28 items measuring physical, sexual and emotional abuse and physical and emotional neglect. Reliability and criterion-related validity have been established [13]. A study in the Netherlands confirmed its five-factor model [82].

The Inventory of Personality Organization (IPO-83-NL, [49]) measures personality organization. The IPO-83 is self-report instrument consisting of 83 items on a 5-point Likert scale, based on Kernberg’s structural model of personality organisation [20]. The Dutch version of the IPO has three main scales (Identity Diffusion, Primitive Defence and Reality Testing) and two supplementary scales (Aggression and Moral Values). The IPO-83-NL has good reliability and validity [11].

The Autism-Spectrum Quotient short form (AQ-10) is derived from the original 50-item AQ [3] by a selection of the 10 items with the best discriminant validity. The questionnaire consists of 10 statements with for every statement four response options: strongly agree, slightly, agree, slightly disagree and strongly disagree. At a cut-point of 6, sensitivity was 0.88, specificity was 0.91 and positive predictive value (PPV) was 0.85.

Finally, narcissistic traits are measured with the Dutch Narcissism Scale (Nederlandse Narcisme Schaal, NNS) that consists of 35 items with a 7-point Likert scale, measuring three dimensions of narcissism: overt (‘centrifugal’) narcissism; covert (‘centripetal’) narcissism and isolation [29]. The construction of the covert narcissism subscale is based on the Dutch translation of the hypersensitive narcissism scale [44] and consists of 11 items, with good reliability (Cronbach’s alpha 0.82). Dutch norms are available.

#### Potential mediators

Potentially general working mechanisms across the group therapies, like group cohesion and group climate, are measured by the Dutch translation of the Group Questionnaire (GQ-NL, [name], Klaassen & De Beurs, in prep.). The GQ, developed by Krogel and colleagues [56], is a 30-item self-report measure that assesses the quality of the therapeutic relationship in a group therapy on a 7-point Likert-scale. The GQ consists of three subscales: Positive Bond, Positive Work and Negative Relationship, with a score for each subscale. All three subscales have good reliability. The GQ also assesses relationship structure using three dimensions: member-leader (working alliance), member–member (group cohesion) and member-group (group climate), and it has shown acceptable criterion validity with the Working Alliance Inventory, Group Climate Questionnaire, Therapeutic Factors Inventory and Empathy Scale [85].

In addition, instruments measuring potential working mechanisms related to schema therapy and psychodynamic therapy are administrated in all three treatments. Change in schema modes (schema therapy) is measured by the Schema Mode Inventory 2 (SMI-2)*,* a modified version of the SMI-1 self-report questionnaire [60]. It consists of 143 items on 18 schema modes that are scored on a 6-point Likert scale and measures to what extent dysfunctional as well as functional schema modes are present. Its subscales have satisfactory to high internal consistency (Cronbach’s α ranges from 0.79 to 0.96) and it is considered to be a useful instrument for assessing modes [61]. Newly formulated modes proved to be appropriate for histrionic, avoidant and dependent personality disorder. In line with Yakin [101], the modes Vulnerable Child and Healthy Adult will be analysed a priori and the Avoidant Protector and Impulsive Child modes exploratory. The complete SMI-2 will be administered at baseline, a shortened version with modes that are relevant for Cluster-C PDs is used for the repeated measures.

For psychodynamic therapy, no commonly applied instruments for measuring mediators were identified in the literature. Therefore, we organized an expert meeting with professional experts in psychodynamic therapy. Four potential mediators were selected: insight, experiential avoidance, self-esteem, and defence style. Insight is measured by a subscale of the Client Task-Specific Change Measure-R (CTSC-R), a 16-item client self-report on a 7-point Likert-type scale [97], designed to measure the extent to which clients are able to identify changes, or newly acquired insight associated with particular sessions. A total score on the scale provides an index of client change following the session. The instrument is validated by Watson et al. [98] and showed good psychometric qualities with high internal consistency. Factor analysis showed the instrument comprises two factors, one dominant factor conceptualized as ‘behaviour change’ and a second minor factor conceptualized as ‘awareness and understanding’. This last factor is used as a measurement for insight in the present study. The psychometric properties of the Dutch version are not known.

Experiential avoidance is measured by The Brief Experiential Avoidance Questionnaire (BEAQ), a 15 item self-report measure. It is the shortened version of the 62-item Multidimensional Experiential Avoidance Questionnaire (MEAQ, [40]. Items are scored on a 6-point Likert Scale. A high score reflects a high level of experiential avoidance. Initial validation of the BEAQ has demonstrated good psychometric qualities. The psychometric qualities of the Dutch BEAQ have recently been studied by Slagter et al. A: Measuring experiential avoidance: psychometric properties of the Dutch multidimensional experiential avoidance questionnaire, in preparation.

Self-esteem is assessed with the Rosenberg Self-Esteem Scale (RSES). The RSES is a widely used 10-item Likert scale for measuring self-esteem. Items are answered on a 4-point scale—from strongly agree to strongly disagree—measuring positive and negative feelings towards the self [75]. The Dutch version of the RSES is found to be a one-dimensional scale with high internal consistency and congruent validity and a Cronbach’s alpha of 0.89 [38].

Finally, adaptive or non-adaptive defence style is measured by a short version of the Developmental Profile Inventory-SV (DPI-SV). The DPI is developed to assess psychodynamic personality functioning, based on the frame of reference of the Development Profile (DP). It consists of 9 subscales representing developmental levels of psychodynamic functioning on three domains: Self, Interpersonal Functioning and Defence/coping style [73]. In this study, only the domain defence/coping style is used. Internal consistencies of the subscales were fair to good, ranging: 0.71 to 0.91 in healthy controls and 0.67 to 0.88 in a patient sample. Mean corrected item-total correlations were good, ranging 0.30 to 0.50. Test–retest reliability was good to excellent, with median ICC levels of 0.86 in healthy controls and 0.81 in the patient sample. The DPI also discriminated between patients and healthy controls in a meaningful way.

In addition, for all approaches, after each therapy session, therapists will indicate which interventions they carried out on a 30-items treatment intervention checklist, the G-FORCE Treatment Intervention List (G-FORCE-TIL). This list has been developed by the authors [92], indicating the core interventions per treatment modality on a dichotomous scale (yes/no). Psychometric qualities of this list will be researched.

